### 2.6. Statistical Consideration

For our primary aim of comparing patient-reported QOL outcomes and treatment sequelae after CIRT with those after surgical treatment, we will use the functional domain of the PROMIS-29 questionnaire. We will specifically compare the mean difference in the functional QOL from before treatment (baseline) to 1 year after the end of treatment, between treatment arms 1 and 2, with a one-sided, two-sample *t* test of independent means. On the basis of previous studies and retrospective clinical data, we conservatively expect a mean decrease in functional QOL of 2 points for treatment arm 1 and 4.6 points for treatment arm 2 (higher than the defined minimal clinically important difference), with an SD of 4 points in both arms. We will obtain 80% power (α = 0.05) to detect significantly improved functional QOL between the 2 treatment arms with 30 patients in each arm (*N* = 90 patients for all 3 arms).

To reduce the likelihood of underpowering the trial because of screening failures, loss to follow-up, death, and other causes that could lower the number of patients reaching the 5-year follow-up study end point, we will recruit an additional 6 patients per treatment arm (*n* = 36 patients per arm, *N* = 108).

Data will be stored and maintained in the external Mayo Clinic REDCap system. Analyses for the primary aim will be completed when all eligible patients have completed the PROMIS-29 questionnaire at baseline and 1 year after the end of treatment. The PROMIS-29 functional score will be calculated, and median, mean, and 95% CI values will be compared between each treatment arm, with one-sided, two-sample *t* tests. Analyses for the secondary aim of determining whether CIRT improves local control in comparison with PT will be completed after the last treated patient has been followed for 3 years. Analysis will be completed for all patients; however, because of the possibility of heterogeneous outcomes resulting from differences in histopathologic findings, analyses of local control will be stratified according to histopathologic characteristics. Subset analyses will also be performed for sacral chordoma vs. non-sacral chordoma. The proportion of patients with local control at 3 years and 95% CI in treatment arms 1 and 3 will be calculated with a one-sided noninferiority test. 

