The Kaplan–Meier method with likelihood ratio tests will be used to evaluate all clinical outcomes, which will include local recurrence, regional progression, distant metastases, progression-free survival, and overall survival, for each treatment arm. Subset and stratified analyses according to histopathologic characteristics will also be conducted for all time-to-event analyses. 

Exploratory analyses of local control between arm 2 and arms 1 and 3, treatment sequelae, and DVH data will be performed with standard logistic regression analysis of acute- (<6 months) and late-onset (≥6 months) treatment sequelae. Area under the receiver operating characteristic curve analyses will be performed for each DVH measure to determine the effect of the treatment modality on treatment sequelae, QOL, local control, and survival.

The participating CIRT centers will have considerable heterogeneity regarding patient selection, treatment prescription, total dose per fraction, target and OAR contouring, OAR constraints, and use of RBE dose calculation models. Therefore, CIRT data will be analyzed separately for each institution. In the unlikely event of marked differences in outcomes among these centers, sub-analyses will be performed, and we will consider publishing data for each (deidentified) institution separately.

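### Kaplan–Meier is prescribed for local, regional and distant failure, so deaths are censored and incidence is overstated, and no estimate is named as governing the local-control aim

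*Protocol article*

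**What the plan says.** All of this stands in section 2.6 (Statistical Consideration) of the protocol article.

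- **Secondary aim, carbon ion (arm 1) against proton therapy (arm 3).** The estimate is given as "The proportion of patients with local control at 3 years and 95% CI", and the test is for noninferiority, one-sided. The analysis "will be completed after the last treated patient has been followed for 3 years".
- **Time-to-event outcomes, each arm.** The Kaplan–Meier "method with likelihood ratio tests will be used to evaluate all clinical outcomes, which will include local recurrence, regional progression, distant metastases", then progression-free and overall survival.
- **Deaths are expected.** The sample size is raised to allow for "screening failures, loss to follow-up, death, and other causes that could lower the number of patients reaching the 5-year follow-up study end point". The remedy given is that "we will recruit an additional 6 patients per treatment arm".

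The section names no competing-risk method. It does not say how the 3-year proportion relates to the Kaplan–Meier curve for local recurrence, and it does not name the model from which the likelihood ratio statistic comes.

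**The concern.** Local recurrence, regional progression and distant metastasis can each be precluded by death. Kaplan–Meier treats a patient who died without the event as if the event could still occur later. It then estimates a net rate, the one that would hold if nobody died of anything else and deaths were independent of recurrence risk. Read as the share of patients who fail, one minus Kaplan–Meier is too high whenever such deaths occur. Progression-free and overall survival do not have this problem, because death is itself an event there.

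The article names Kaplan–Meier for these endpoints outright, so this is a stated choice and not a detail left to an unseen analysis plan.

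Two further points follow. First, a 3-year proportion and a Kaplan–Meier curve can give different local-control figures for arms 1 and 3 from the same data, and nothing says which one answers the secondary aim. Secondly, Kaplan–Meier is nonparametric, whereas a likelihood ratio test compares fitted models, so the test is not defined until the model is named.

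The Discussion says the trial should supply benchmark local-control rates for designing later Phase III studies. Someone reusing such a rate needs to know whether it is a net rate or an actual incidence.

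**Working it through.** **The plan's own figures.** No sample size, margin or expected rate is given for local control, so there is no local-control figure to reproduce. The only sample size is for the functional quality-of-life endpoint (difference 4.6 − 2 = 2.6, SD 4, one-sided 0.05, 80% power). It reproduces: 2 × (1.645 + 0.842)² × 4² / 2.6² = 29.3, so 30 per arm. It does not bear on this point. The attrition allowance is 6/36 = 16.7%.

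**Formulas.** Constant cause-specific hazards are assumed: a for local recurrence, b for death without recurrence, time t in years.

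- 1 − KM = 1 − exp(−a·t)
- Cumulative incidence, CIF = a/(a + b) × [1 − exp(−(a + b)·t)]

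**Step 1: the document's allowance, read entirely as competing deaths.** Assume a = 0.10. At 3 years, 1 − KM = 1 − exp(−0.30) = 25.9%.

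- 16.7% dead by 5 years: b = −ln(5/6)/5 = 0.0365. CIF = 0.10/0.1365 × [1 − exp(−0.409)] = 24.6%. Gap 1.3 points.
- 16.7% dead by 3 years: b = −ln(5/6)/3 = 0.0608. CIF = 0.10/0.1608 × [1 − exp(−0.482)] = 23.8%. Gap 2.1 points.

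**Step 2: a range of assumed death hazards, a = 0.10.**

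| b per year | 1 − KM, 3 y | CIF, 3 y | Gap | 1 − KM, 5 y | CIF, 5 y | Gap |
|---|---|---|---|---|---|---|
| 0.05 | 25.9% | 24.2% | 1.8 | 39.3% | 35.2% | 4.2 |
| 0.10 | 25.9% | 22.6% | 3.4 | 39.3% | 31.6% | 7.7 |
| 0.15 | 25.9% | 21.1% | 4.8 | 39.3% | 28.5% | 10.8 |

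Gaps are in percentage points, from unrounded values. The 5-year columns concern the Kaplan–Meier curves only, since the secondary analysis is at 3 years.

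**Step 3: other assumptions at 3 years.** With net recurrence of 10–30% and net death of 5–40%, the gap runs from 0.2 to 6.2 points. At 20% recurrence it is 0.5 points with 5% deaths and 4.2 points with 40%.

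**Step 4: why the governing estimate must be named.** Take 20% net recurrence and 20% net death at 3 years, so a = b and CIF = 0.5 × (1 − 0.8 × 0.8) = 18.0%.

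- Kaplan–Meier local control: 80.0%
- Proportion, deaths without recurrence counted as controlled: 1 − 0.18 = 82.0%
- Proportion, such deaths excluded: 0.64/(0.64 + 0.18) = 78.0%
- Proportion, such deaths counted as failures: 64.0%

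**Scale.** The 95% CI half-width for 80% at n = 30 is 1.96 × √(0.8 × 0.2/30) = 14.3 points.

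**The case against.** The strongest reply is that the two analyses have different jobs. The proportion serves a noninferiority test of arms 1 and 3, and Kaplan–Meier describes each arm over time. The 3-year proportion may even be read off the Kaplan–Meier curve, since the article never calls it a crude count. How deaths enter it may be set out in the full protocol or analysis plan, which are not shown. Kaplan–Meier with deaths censored is also a legitimate estimate of net local control, and section 2 motivates the aim by biological effectiveness, for which a cause-specific comparison is reasonable.

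Much of this stands. The passages are unreconciled and not strictly contradictory, and Kaplan–Meier misleads only when read as actual incidence. It does not settle which figure answers the secondary aim, because the Kaplan–Meier sentence covers every arm, nor does it supply the missing model.

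Three stronger readings are tempting, and the article does not support them.

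- **That every local-control rate will be biased.** With complete 3-year follow-up and deaths without recurrence counted as controlled, the simple proportion equals one minus the cumulative incidence.
- **That local control has three competing estimators.** "Exploratory analyses of local control between arm 2 and arms 1 and 3, treatment sequelae, and DVH data will be performed with standard logistic regression" looks like a third, but the sentence goes on to make acute and late treatment sequelae the modelled outcome. It is exploratory, and its local-control comparison is a different one (arm 2 with arms 1 and 3).
- **That arm 1 will have more deaths than arm 3 because of larger tumours.** Section 2 makes the tumour-size statement about carbon ion against surgery, not against proton therapy. The Discussion notes that arm 1 may differ in health care access and baseline characteristics, but gives no direction for death or loss.

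**Conclusion.** The point holds in a limited form. Kaplan–Meier is the wrong stated estimator if local recurrence, regional progression and distant metastasis are to be reported as rates of failure. The estimate that governs the secondary aim is not identified, and the likelihood ratio test lacks its model.

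The size cannot be fixed from the article. At a recurrence hazard of 0.10 per year it is about 1 to 2 points at 3 years if the whole 6/36 allowance were competing deaths. That is a generous reading, because the allowance also covers screening failures and loss to follow-up. It reaches about 5 points at a death hazard of 0.15 per year. All of these figures rest on constant hazards and assumed rates, and all are small beside a half-width near 14 points. The 18-point spread in step 4 (82% to 64%) shows what an unstated counting rule could do. It is not a predicted bias, because no such rule is stated and one may exist elsewhere.

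The change is worth making because it is cheap and the rates are meant to serve as benchmarks. It does not threaten the trial's primary comparison.

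**What to change.** 1. Make the 3-year cumulative incidence of local recurrence the single governing estimate for the secondary aim: Aalen–Johansen estimator, death without recurrence as a competing event, loss to follow-up censored. Report the arm 1 minus arm 3 difference with its confidence interval, and base the planned noninferiority test on it. If a 3-year local-control proportion is also shown, define it as one minus this quantity.
2. Estimate regional progression and distant metastasis the same way.
3. Name one test for arm comparisons of these endpoints: Gray's test, or a cause-specific log-rank or Cox test. Censoring deaths is proper for comparing cause-specific hazards. Allow at most one or two covariates in a Cox model: about 25% recurrence in 60 patients is only 0.25 × 60 = 15 events.
4. Keep Kaplan–Meier for progression-free and overall survival, with a log-rank test or a likelihood ratio test from a named Cox model.

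**Cost.** Analysis wording and slightly more analysis work. Recurrence, death and follow-up dates are already needed for the planned survival analyses, so no new data are required.

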## 2. Research Methods and Analysis

The purpose of the PROSPER study (ClinicalTrials.gov, NCT05033288) was to compare patient-reported outcomes, adverse events/treatment sequelae, and local tumor control for bone/soft tissue sarcoma involving the pelvic bone, among three treatment arms: (1) CIRT, (2) surgical treatment, and (3) PT (Figure 1). 

The primary aim of the study is to compare patient-reported health-related QOL outcomes and treatment sequelae after CIRT with those after surgical treatment. We acknowledge that the CIRT and surgical treatment arms will have considerably different disease-specific characteristics (e.g., tumor stage, size, and extent), with a disproportionate number of patients who undergo CIRT having larger and higher-stage tumors involving the sacral plexus. However, if the functional outcomes and treatment sequelae data show an advantage for CIRT, despite these differences, then CIRT would most likely yield the same, or even better, favorable functional outcomes when comparing the two treatment arms containing disease severity-matched patient cohorts.

The secondary aim of the study is to determine whether CIRT improves local control in comparison with PT. This aim was chosen because CIRT is considered to be more biologically effective than radiotherapies with a lower LET (i.e., photon therapy or PT) for treating radioresistant tumors and may reduce the risk of local recurrence. 

The PROSPER study was designed as a prospective, parallel cohort study. Although a randomized study would provide a higher level of evidence, several feasibility and administrative challenges would arise with a randomized trial. Specifically, randomization between the surgical treatment and definitive treatment with the CIRT or PT arms would have been problematic. Even the ongoing SACRO trial, which has enrolled more than 100 patients, could not randomly assign patients, and all patients were treated in the prospective cohorts. 

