### 2.5. Follow-Up

Standard follow-up will include medical history and physical examination with Eastern Cooperative Oncology Group Performance Status scores at approximately 3, 6, 12, 24, 36, 48, and 60 months. Magnetic resonance imaging of the pelvis will be preferred, but computed tomography or positron emission tomography/computed tomography will be acceptable if the patient is unable to undergo magnetic resonance imaging. Imaging findings, treatment sequelae, and PROMIS-29 and EORTC QLQ-CR29 responses will be collected at each follow-up examination.

Assessments of treatment sequelae will include the following Common Terminology Criteria for Adverse Events v5.0: gastrointestinal tract (diarrhea, nausea, vomiting, perforation, stenosis, ulcer, colitis, obstruction, fistula, fecal incontinence, and necrosis), urinary tract (dysuria, fistula, incontinence, urgency, and retention), musculoskeletal (osteonecrosis, soft tissue necrosis, fracture, muscle weakness, lower limb, extremity pain, pelvic pain, lymphedema, soft tissue fibrosis, and gait disturbance), sexual function (dyspareunia in women and erectile dysfunction in men), and nervous system (motor neuropathy, sensory neuropathy, phantom pain, and radiculitis) disorders.

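### Standard logistic regression is fixed for the exploratory sequelae analyses at 30 patients per arm, and for sequelae with true rates of about 5% or less it will often give no usable odds ratio

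*Protocol article*

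**What the plan says.** Section 2.6 of the protocol article names the method. It labels the work on sequelae as exploratory and says that these analyses "will be performed with standard logistic regression analysis"; sequelae are split at six months into acute and late. No penalised or exact method is mentioned, and no test or interval is specified for this model. The likelihood ratio tests in the same section belong to the Kaplan–Meier outcomes.

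The sample size comes from the primary end point, the one-year change in PROMIS-29 function: 80% power "with 30 patients in each arm". To cover losses, "we will recruit an additional 6 patients per treatment arm", which makes 36.

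Section 2.5 lists the CTCAE items. Among the gastrointestinal ones are "perforation, stenosis, ulcer, colitis, obstruction, fistula, fecal incontinence, and necrosis". The list also holds items that could well be frequent, such as pain, gait disturbance and neuropathy.

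Section 2 puts sequelae in the primary aim, which is to compare "patient-reported health-related QOL outcomes and treatment sequelae after CIRT with those after surgical treatment". In section 2.6 that aim is tested only on PROMIS-29 function.

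**The concern.** In ordinary usage, standard logistic regression means unpenalised maximum likelihood. That method breaks down when one arm has no events, because the fitted log odds ratio then runs off to infinity. Its standard error grows without bound and the Wald statistic goes to zero. The breakdown is most likely when one modality avoids a harm that another causes, and part of the rationale for CIRT is that it may reduce sequelae.

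The stake is the quality of reporting. The Discussion expects the study to supply benchmark figures for sequelae that could help design later phase III trials. An infinite odds ratio with an unusable interval cannot serve as a benchmark, and a Wald p value near 1 beside a contrast of 0 v 8 events would mislead a reader.

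**Working it through.** **Inputs from the article (section 2.6).** 30 evaluable and 36 recruited patients per arm, three arms. For the primary end point: difference 4.6 − 2 = 2.6 points, SD 4, one-sided α = 0.05, power 80%.

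**Assumed.** True sequela rates, shown as a range because none is given; a two-sided 0.05 level for sequelae, since none is stated; one binary outcome per model, compared between arms.

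**1. The plan's own figure.** n = 2 × (1.645 + 0.842)² × (4/2.6)² = 2 × 6.18 × 2.37 = 29.3, so 30 per arm. Power at 30 by the noncentral t is 80.04%. The 30 is reproduced. It was not derived for sequelae.

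**2. Chance of an empty arm.** For one arm, (1 − p)ⁿ. For at least one of three arms at a common rate, 1 − [1 − (1 − p)ⁿ]³.

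| True rate | One arm, n = 30 | Any of three, n = 30 | Any of three, n = 36 |
|---|---|---|---|
| 3% | 0.40 | 79% | 70% |
| 5% | 0.21 | 52% | 40% |
| 10% | 0.04 | 12% | 7% |

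Example at 5%: 0.95³⁰ = 0.215, and 1 − 0.785³ = 0.516.

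**3. What happens with an empty arm: 0/30 v 8/30.**
- Maximum likelihood: the software stops at a log odds ratio of about 22.6 in size with SE about 14,508, so Wald p = 0.999. The true estimate is infinite.
- Likelihood-ratio test, same model: p = 0.0004.
- Fisher exact: p = 0.005.
- Firth: for a 2×2 table the estimate adds 0.5 to each cell, giving OR = (0.5 × 22.5)/(30.5 × 8.5) = 0.04; penalised likelihood-ratio p = 0.002.

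**4. Rejection rates.** Exact enumeration of all 31 × 31 outcomes at n = 30, two-sided 0.05, with Wald counted as not significant when a cell is zero.

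| True rates | Wald | Likelihood ratio | Firth | Fisher |
|---|---|---|---|---|
| 2% v 20% | 15% | 74% | 64% | 41% |
| 5% v 25% | 34% | 66% | 58% | 44% |
| 10% v 40% | 73% | 82% | 79% | 71% |

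Under equal rates, the likelihood-ratio test rejects 8.3% of the time at 5% and 7.5% at 10%. Firth rejects 2.7% and 4.1%, and 4.6% at 20%. So part of the likelihood-ratio test's apparent advantage is inflated error. A single table shows this too: 0 v 3 events gives likelihood-ratio p = 0.038 against Fisher 0.24.

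**The case against.** The case on the other side is substantial, and most of it limits the point.

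- **The analysis is exploratory.** This stands. A reader might infer from the primary aim's wording that the primary comparison is at risk. It is not: that aim is tested with a t test on PROMIS-29 function, and no primary or secondary test, sample size or error rate uses the logistic model.
- **The plan names a model, not a test.** This stands. A reader might infer that standard logistic regression would report the clearest contrasts as non-significant. That holds only for a Wald test, which the article never names; the likelihood-ratio test from the same model has more power than Firth in the table above. It is no clean remedy, because it is liberal when events are sparse and does not make the estimate finite. Nor does the article say that such results would be discarded.
- **No event rates are given.** This stands. That empty arms will be common across the whole list cannot be shown. It follows at rates of about 5% or less and fails at 10% or more.
- **The unit of analysis is open.** This stands. The article does not say that each CTCAE item is modelled separately; grouping by organ system would rarely leave an arm empty. It also does not say that DVH measures enter a joint model with treatment arm, so the idea that they would worsen separation is not supported.
- **Sparse-data handling belongs in a fuller document.** This stands in part. A fallback may exist there. But the article fixes a method by name, and that name points to the ill-suited version.
- **Little is rescued when events are rare everywhere.** This is true. At 2% v 10%, Firth power is only 20% and Fisher 4%; the limit there is sample size.

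**Conclusion.** The point holds in a limited form. For any sequela modelled on its own with a true rate of about 5% or less, an empty arm is likely at 30 per arm (52% at 5%, 79% at 3%, for any of three arms). The named method then yields no finite odds ratio and no usable Wald interval. If the Wald test is used, power at 2% v 20% is 15% against 64% for Firth. At 10% v 40% the gap shrinks to 73% against 79%, so frequent sequelae are little affected.

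The conclusion rests on assumed event rates, separate modelling of items, a two-sided 0.05 level, and reading the named method as unpenalised maximum likelihood. It concerns an exploratory analysis. It does not show that the trial's main comparison is compromised or that real differences in sequelae would necessarily be missed. It is a cheap improvement to a stated method.

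**What to change.** In section 2.6, for the sequelae models, replace standard logistic regression with Firth penalised logistic regression and profile penalised-likelihood 95% CIs, with Fisher's exact test or exact logistic regression as a check. Add that where an arm has no events, the result reported is the risk difference with an exact or score interval. If a fuller protocol or analysis plan already contains such a rule, align the wording with it.

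The cost is a phrase or two of text, slight shrinkage of the estimates and a little more analysis work. No further data or patients are needed.

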**Abstract:**

Surgical treatment of pelvic sarcoma involving the bone is the standard of care but is associated with several sequelae and reduced functional quality of life (QOL). Treatment with photon and proton radiotherapy is associated with relapse. Carbon ion radiotherapy (CIRT) may reduce both relapse rates and treatment sequelae. The PROSPER study is a tricontinental, nonrandomized, prospective, three-arm, pragmatic trial evaluating treatments of pelvic sarcoma involving the bone. Patients aged at least 15 years are eligible for inclusion. Participants must have an Eastern Cooperative Oncology Group Performance Status score of two or less, newly diagnosed disease, and histopathologic confirmation of pelvic chordoma, chondrosarcoma, osteosarcoma, Ewing sarcoma with bone involvement, rhabdomyosarcoma (RMS) with bone involvement, or non-RMS soft tissue sarcoma with bone involvement. Treatment arms include (1) CIRT (*n* = 30) delivered in Europe and Asia, (2) surgical treatment with or without adjuvant radiotherapy (*n* = 30), and (3) proton therapy (*n* = 30). Arms two and three will be conducted at Mayo Clinic campuses in Arizona, Florida, and Minnesota. The primary end point is to compare the 1-year change in functional QOL between CIRT and surgical treatment. Additional comparisons among the three arms will be made between treatment sequelae, local control, and other QOL measures.

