In the PROSPER study, patients with unresectable tumors will be enrolled in the trial, although they will not be eligible to be randomly assigned to the surgical treatment arm. Although randomization between the CIRT and PT treatment arms would potentially be possible, the logistics of randomizing these arms would still pose challenges. The PROSPER study protocol was activated at all 3 Mayo sites in 2022: at Mayo Clinic in Florida on 20 January, Mayo Clinic in Arizona on 14 February, and Mayo Clinic in Minnesota on 1 June. The participating CIRT sites are currently preparing to activate the trial. To date, no patients have been enrolled in the PROSPER study. We anticipate that the enrollment period will require up to 36 months for accrual. 

Mayo Clinic will enroll most of the patients in the trial but will not have the ability to treat patients with CIRT until 2027, when Mayo Clinic in Florida will open its CIRT center to patients. Although Mayo Clinic investigators could send patients to Europe or Asia to receive CIRT, treatment costs and travel restrictions would be challenging because the reimbursement of costs associated with sending patients abroad is currently unresolved for CIRT. Indeed, during the development of the PROSPER study, a randomized trial led by the University of Texas Southwestern Medical Center assessing CIRT vs. intensity-modulated radiotherapy/PT treatment of patients with pancreatic cancer (NCT03536182) was opened, closed, and withdrawn when the COVID-19 pandemic restricted travel, as well as the ability to randomly assign US patients to centers with CIRT in Europe and Asia.

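### Treatment sequelae sit in the primary aim but are analysed only as exploratory, and the stated method for late-onset sequelae takes no account of time at risk

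*Protocol article*

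**What the plan says.** **Rank of sequelae.** Section 2 states: "The primary aim of the study is to compare patient-reported health-related QOL outcomes and treatment sequelae after CIRT with those after surgical treatment". Section 2.6 repeats the aim and in the same sentence narrows it to one instrument: "primary aim of comparing patient-reported QOL outcomes and treatment sequelae after CIRT with those after surgical treatment, we will use the functional domain" of PROMIS-29. The t test, the sample size and the trigger for the primary analysis all concern that score. The Abstract is narrower still: "The primary end point is to compare the 1-year change in functional QOL between CIRT and surgical treatment". It then adds: "Additional comparisons among the three arms will be made between treatment sequelae, local control, and other QOL measures". Later in section 2.6 the sequelae analysis is labelled exploratory.

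**Use of sequelae.** Section 2 concedes that the CIRT arm will have larger and higher-stage tumours. It argues that "if the functional outcomes and treatment sequelae data show an advantage for CIRT, despite these differences", CIRT would probably do as well or better in cohorts matched for severity.

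**Method.** Sequelae are to be analysed by "standard logistic regression analysis of acute- (<6 months) and late-onset (≥6 months) treatment sequelae". The Kaplan–Meier outcomes listed in the paragraph before are oncologic only.

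**Follow-up.** Section 2.5 gives one visit schedule for all arms, from 3 to 60 months, with sequelae recorded at each visit. Section 2.6 adds 6 patients per arm partly because death and loss may keep patients from reaching 5 years. Section 2 allows up to 36 months for accrual. It reports the three Mayo campuses as activated in 2022, while for arm 1 "The participating CIRT sites are currently preparing to activate the trial"; no patient had been enrolled in any arm.

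**The concern.** There are two linked problems.

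First, a reader cannot tell whether a difference in sequelae would count as a primary result. The PROMIS-29 functional score does not measure the listed CTCAE events, so the sequelae half of the primary aim has no test and no power behind it. Section 2.5 lists about 30 CTCAE terms, and the article singles out none for the primary comparison. If sequelae keep their place in the primary aim and in the section 2 argument, an exploratory result could be reported with the weight of a primary one.

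Second, logistic regression on whether a late event occurred treats a patient observed for one year and a patient observed for five as equally informative. The late window starts at 6 months and the article gives it no end other than the last scheduled visit. Patients who die, are lost or enter late have less time in which to show an event. If that happens more in one arm, the odds ratio mixes the rate of sequelae with the length of observation. The acute window (<6 months) is little affected.

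**Working it through.** **Step 1. What the sample size covers.** Inputs from section 2.6: expected declines of 2 and 4.6 points, so a difference of 2.6; SD 4; one-sided α 0.05; 80% power.

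n per arm = 2 × (1.645 + 0.842)² × (4/2.6)² = 2 × 6.18 × 2.367 = 29.3, rounded up to 30. An exact calculation with the noncentral t gives 29.97 per arm and 80.0% power at 30. The plan's figure reproduces. It concerns PROMIS-29 function only.

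**Step 2. What 30 per arm would give for sequelae.** The documents give no sequelae rates, so the rates below are assumptions. Normal approximation for two proportions, pooled variance under the null, one-sided α 0.05:

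| Assumed proportions | Power at 30 per arm | n per arm for 80% power |
|---|---|---|
| 50% vs 30% | 47% | 74 |
| 40% vs 20% | 52% | 64 |
| 50% vs 25% | 64% | 46 |
| 60% vs 30% | 77% | 33 |

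Under these assumptions the trial is not sized for sequelae as a primary comparison. This argues for resolving the contradiction by narrowing the aim, not by promoting sequelae.

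**Step 3. Effect of leaving out time at risk: unequal follow-up.** Assume the same constant late-event rate h in both arms (no treatment effect), counted from 6 months. The proportion with a late event by follow-up T years is 1 − exp(−h × (T − 0.5)).

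- h = 0.10, T = 3: 1 − exp(−0.25) = 22.1%
- h = 0.10, T = 4: 1 − exp(−0.35) = 29.5%. The gap is 7 points and the odds ratio (0.221/0.779)/(0.295/0.705) = 0.68.
- h = 0.20, T = 3 vs 4: 39.3% vs 50.3%, a gap of 11 points.
- Equal T: gap 0, odds ratio 1.0.

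With gaps in follow-up of 0.5 to 1.5 years from a base of 3 years, the spurious difference is 4 to 11 points at h = 0.10 and 6 to 16 points at h = 0.20. Its sign follows whichever arm is observed for less time.

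**Step 4. Effect with a common schedule but unequal exit.** Assume all patients are scheduled to 60 months (4.5 years at risk after month 6), the same h in both arms, and exit by death or loss at rate m. The proportion with an observed event is h/(h + m) × (1 − exp(−(h + m) × 4.5)).

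- h = 0.10, m = 0.20: 0.333 × (1 − exp(−1.35)) = 24.7%
- h = 0.10, m = 0.10: 0.500 × (1 − exp(−0.90)) = 29.7%; odds ratio 0.78
- h = 0.30, m = 0.20 vs 0.10: 53.7% vs 62.6%; odds ratio 0.69
- Equal m: odds ratio 1.0

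A common schedule therefore does not remove the problem if exit differs. None of the rates or gaps in steps 3 and 4 comes from the documents.

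**The case against.** The strongest reply accepts that the wording of the aim needs tidying but holds that the rest goes beyond the text. Several parts of it stand.

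- **Unequal follow-up is not stated.** A reader might infer from the site activation dates that surgery and proton patients will be observed longer and that the late analysis will therefore favour CIRT. The documents do not support this as fact. One schedule applies to all arms, no patient had been enrolled anywhere, accrual by arm is not given, and no data cut for sequelae is stated. If every patient is analysed after 60 months, staggered entry creates no difference.
- **The direction is open.** More deaths in arm 1 would lower its count of late events, but larger tumours involving the sacral plexus could raise it.
- **Section 2 sets no decision rule.** A reader might take it as a formal rule for declaring CIRT better. It is an interpretive argument about confounding, and it asks for an advantage in function and sequelae together, so one favourable CTCAE term would not meet it.
- **Outcome coding, grade threshold and horizon** may sit in the full protocol or SAP. Ever/never coding is the natural reading of logistic regression on two windows, but it is not the article's wording. Exploratory analyses do not ordinarily carry error control.

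Two things survive. The conflict over the rank of sequelae is between statements in the article, and an unseen SAP cannot make them agree. And the article does not leave the late-onset method open: it names one that carries no time at risk, in a trial where it expects deaths and losses before 5 years.

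**Conclusion.** The point holds in limited form. The contradiction is certain: sequelae are primary in the aim (sections 2 and 2.6), additional in the Abstract and exploratory in the analysis, with power only for PROMIS-29 function. The sample size itself contains no error.

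The weakness of the late-onset method is conditional. It biases the comparison only if time under observation differs between arms, through death, loss or staggered entry. The documents give neither the size nor the direction of such a difference. The 22% against 30% illustration rests on an assumed rate of 0.10 per year and assumed follow-up of 3 and 4 years, and the effect is zero when observation is equal. The primary test of PROMIS-29 function is untouched. The change is worth making because it is cheap and because section 2 leans on the sequelae result.

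**What to change.** 1. In sections 2 and 2.6, restrict the primary aim to the 1-year change in PROMIS-29 function, arm 1 against arm 2, as the Abstract already has it.
2. State sequelae as a secondary or supportive comparison, with the same rank in the Abstract, section 2 and section 2.6, and say in the section 2 argument that the sequelae data are supportive.
3. Replace logistic regression for late-onset sequelae by time to first event, reported as cumulative incidence with death as a competing event; or fix one horizon common to all arms. The first handles loss and staggered entry by censoring. The second deals with staggered entry, but patients lost before the horizon still need a stated handling. Under either, an arm with more deaths will show fewer sequelae, so deaths should be shown alongside and, for time to event, the cause-specific hazard as well.

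The choice of event, grade and horizon is for the sponsor; the article gives no basis for prescribing one.

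Cost: the primary aim claims less, and there is slightly more analysis work. No new data are needed, since sequelae are already collected at every follow-up visit; event times will be known to the visit interval unless onset dates are recorded.
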